**Fig. 1 Fig1:**
[figure not shown]
Subject distribution among groups in the study

### Blinding

This is an open-label trial. Trial participants, investigators, care givers, outcome assessors, and date analysts are not blinded to group assignment.

### Interventions

Participants will be randomized into two equal groups: statin (atorvastatin) or control group as soon as clinical conditions permit. The statin group will be required to take atorvastatin 20 mg daily (known to be a safe dose effective in lipid-lowering and anti-inflammatory activity [19–21]), and the control group will be required to not take statins during study period. Atorvastatin will be provided by Pfizer (New York, USA).

The scheduled duration of treatment is the duration of the hospital stay unless a serious adverse event occurs or the participant quits. The detailed study schedule is listed in Fig. 2.

**Fig. 2 Fig2:**
[figure not shown]
Schedule of enrollment, interventions and assessments for the trial

### Data handling and record keeping

Once the subjects are formally enrolled, case report forms (CRFs) will be established. The CRF will be used to record data for all participants. This task will be completed by the researchers, who will also enter the data into an electronic database, and CRFs will be double entered.

### Withdrawal

Patients may be withdrawn from the study for any of the following reasons:
They may choose to withdraw for any reason;They have abnormalities in ALT/AST (> 3 times upper limit of normal) after drug administration;The patient wants to accept other kinds of statins;Other situations: based on the investigator’s discretion, the patient is no longer eligible for the study for any reason.

### Sample size

Preliminary data indicates that acute aortic dissection is associated with an in-hospital mortality of 27.4% [18]. We predict that treatment with atorvastatin will reduce mortality to 12.4%, while no change will be seen in the control group, which will show a mortality of 27.4%. To obtain 90% power to demonstrate a statistically significant difference (two-sided test, alpha = 0.05) between the two treatments, we anticipate that 307 participants will need to be recruited with154 for the control group and 153 for the statin group. This corresponds to a hazard ratio of 0.4135. Given the possibility of exclusion or lost follow-ups, an increase of 20% will be required for the sample size, bringing the sample size to 192 per arm for a total of 384 participants to be enrolled. All calculations are done through PASS software (NCSS, America, version 11), using the log-rank test, Freedman method.

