## Background

Acute aortic dissection (AAD) is relatively uncommon but is considered a life-threatening, potentially fatal condition [1]. A recent International Registry of Acute Aortic Dissection (IRAD) study shows that 87–90% of AAD is treated surgically, and drug treatment only accounts for 7–8%. Nevertheless, the IRAD study indicates that in-hospital surgical mortality for AAD remains approximately 20% [2], indicating improvement of the long-term outcome of patients with aortic diseases requires further optimization [3]. However, in addition to strict control of blood pressure and heart rate, the effect of other drugs on AAD is still controversial and lacking strong clinical evidence.

Dyslipidemia and atherosclerosis are important risk factors for AAD [4]. Lipid deposition in the vascular wall can lead to local inflammation [5] and promote the release of inflammatory mediators that destroy the vascular wall, leading to aortic dissection (AD) [6]. Statins are classical drugs for lowering low-density lipoprotein cholesterol (LDL-C) levels, and are both anti-inflammatory and anti-atherosclerotic [7], suggesting that statins may delay progression of AAD.

Recent reports have shown that statins have anti-inflammatory effects and can decrease morbidity and mortality following surgical repair of aneurysms in patients with abdominal aortic aneurysms and aneurysm expansion [8–11], and several experimental studies demonstrate the protective effect of statins [12–14]. A retrospective study showed that patients with AAD who used statins had a significantly better prognosis than those who did not [15]. Also, a prospective and randomized comparative study of patients with uncomplicated acute type B aortic dissection (ABAD) showed that pitavastatin treatment has a suppressive effect on aortic arch dilatation [3]. However, a retrospective review points out that statins do not improve in-hospital and long-term outcomes in patients with Stanford B aortic dissection treated with endovascular aortic repair [16]. Although these studies have explored the effects of statins on aortic disease [3, 14–17], the results remain controversial. The aim of this randomized clinical trial study is to understand the efficiency of atorvastatin on in-hospital mortality of patients with AAD. We propose that AAD patients treated with statins will have lower in-hospital mortality than patients without.

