### Criteria

Inclusion criteria:
Patient agrees to cooperate with all study procedures;Age > 20 years old;Physical status permits oral medication;Cholesterol < 5.1 mmol/l, triglyceride < 1.7 mmol/l;Provision of written informed consent.

Exclusion criteria:
Liver dysfunction: alanine aminotransferase (ALT)/aspartate aminotransferase (AST) > 3 times the normal value;Breast-feeding or pregnancy (for women of child-bearing age, the human chorionic gonadotropin level will also be measured before drug administration);Previous history of coronary atherosclerotic heart disease;Statins used within 6 months before inclusion;Participation in another clinical trial within 6 months;Allergy to statins.

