### Limitations

The limitations of this study should also be considered, including confirming that patients can diet normally before being formally included in the study, which may exclude critically ill patients whose deaths would occur within several hours of onset and would not be reported, thereby reducing the mortality rate reported for AAD. For surgical patients, preoperative fasting is often required, and patients in this group often need to wait until a normal diet is restored after surgery before they can be included in the study, which may also exclude critically ill patients whose deaths would occur before normal dieting is restored and would not be reported, thereby reducing the mortality rate reported for AAD. Considering the safety of atorvastatin, a low dose of 20 mg/day will be used in this study, and any possible effects may not be very significant. This is an exploratory study. If there is no significant positive effect at the end, but the results suggest it is safe and does not increase mortality, effectiveness may be observed by subsequently increasing the dose. We will explore the most appropriate dose in the next study. As atorvastatin is a tablet drug, we have sought several companies including Pfizer for suitable tablet placebo, while we failed to find out such placebo that are totally the same in color, shape, smell, and taste. So this is an open-label trial which may weaken its persuasiveness. However, if the results of this study are positive, it will provide evidence in reducing in-hospital mortality in patients with AAD, we will continue to carry out multicenter double-blind study to verify the results of this experiment.

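### The unconditional 90% power rests on a 27.4% control mortality for acute aortic dissection in general and is not supported for the patients this trial enrols

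*Protocol article*

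**What the plan says.** The Sample size section fixes the control rate with "Preliminary data indicates that acute aortic dissection is associated with an in-hospital mortality of 27.4% [18". It adds "We predict that treatment with atorvastatin will reduce mortality to 12.4" per cent, with the control group staying at 27.4%, and "This corresponds to a hazard ratio of 0.4135". The power claim is "To obtain 90% power to demonstrate a statistically significant difference (two-sided test, alpha = 0.05", by the log-rank test with the Freedman method. This gives 307 participants, raised by 20% to 384 to cover exclusion or loss to follow-up.

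The population enrolled is narrower than the disease at large. An inclusion criterion under Criteria is "Physical status permits oral medication". Under Follow-up, observation runs from randomisation to death, discharge or day 30. The Limitations section explains that patients who die within hours of onset may never enter. Surgical patients often enter only once they are eating normally after the operation, "which may also exclude critically ill patients whose deaths would occur before normal dieting is restored and would not be reported". That section states twice that the result is lower mortality.

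One other mortality figure appears, in Background, from a registry: "in-hospital surgical mortality for AAD remains approximately 20" per cent.

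**The concern.** The control rate and the enrolled population do not match. The 27.4% is attached to acute aortic dissection as such. The trial counts deaths only from randomisation, after oral intake has become possible. The protocol recognises this selection and gives its direction, but treats it only as affecting the mortality that will be reported. It never carries it into the power calculation.

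Power for a mortality comparison is driven by the number of deaths. If control mortality after randomisation is below 27.4%, the same number of patients yields fewer deaths, and the 90% no longer describes the design. Both the Limitations and the Discussion set out what will follow if no significant benefit is found. The chance of missing the planned effect is therefore a figure the trial relies on.

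**Working it through.** **Inputs (Sample size section):** control 27.4%, atorvastatin 12.4%, two-sided alpha 0.05, power 90%, 154 + 153 = 307 evaluable, 384 enrolled (192 per arm). The primary test, a chi-square, comes from Statistical and analytical plans.

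**Reproducing the plan's figures**

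- Hazard ratio: ln(1 − 0.124)/ln(1 − 0.274) = (−0.1324)/(−0.3202) = 0.4135, as stated.
- Freedman deaths: (1.960 + 1.2816)² × [(1 + 0.4135)/(1 − 0.4135)]² = 10.51 × 5.81 = 61.0.
- Patients: 61.0 / [(0.274 + 0.124)/2] = 61.0 / 0.199 = 306.6, so 307.
- Inflation: 307/(1 − 0.20) = 383.75, so 384.

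The formula and the arithmetic are right. The question is only the 27.4% that goes in.

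**Lowering the control rate at the same hazard ratio**

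For control rate c:

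- treated rate t = 1 − (1 − c)^0.4135
- expected deaths d = N(c + t)/2
- Freedman power = Φ(√d × (1 − 0.4135)/(1 + 0.4135) − 1.960)

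Example at c = 0.20, N = 307: t = 0.0881, d = 44.2, power = Φ(6.65/2.41 − 1.96) = Φ(0.80) = 79%.

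The planned chi-square test (no continuity correction) was checked by summing exact binomial probabilities at 154/153 and 192/192. Each power cell is Freedman / exact chi-square.

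| Control rate | Treated rate | Deaths, N = 307 | Power, N = 307 | Deaths, N = 384 | Power, N = 384 |
|---|---|---|---|---|---|
| 27.4% | 12.4% | 61.1 | 90.0 / 91.9% | 76.4 | 95.2 / 96.3% |
| 25% | 11.2% | 55.6 | 87.2 / 89.2% | 69.5 | 93.3 / 94.6% |
| 22% | 9.8% | 48.8 | 82.6 / 84.9% | 61.0 | 90.0 / 91.6% |
| 21% | 9.3% | 46.5 | 80.8 / 83.1% | 58.1 | 88.6 / 90.3% |
| 20% | 8.8% | 44.2 | 78.8 / 81.1% | 55.3 | 87.0 / 88.8% |
| 15% | 6.5% | 33.0 | 66.4 / 68.5% | 41.3 | 76.0 / 78.2% |
| 10% | 4.3% | 21.9 | 49.3 / 50.3% | 27.4 | 58.4 / 60.2% |

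Only 27.4% and about 20% are printed in the protocol. The other control rates are assumed for illustration.

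At 307, the Freedman calculation reaches 90% only at 27.4%. At 384 with nobody lost, it holds 90% down to about 22%, and the chi-square to about 21%. Sizing on the log-rank test while analysing by chi-square makes only about two points' difference and is not the issue.

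**The case against.** The strongest reply is that 307 is the pessimistic sample. The outcome is death in hospital, observed daily to death, discharge or day 30, and the analysis is by intention to treat. Losing the vital status of a fifth of inpatients is unlikely, although the Withdrawal section leaves room for some loss. With nearly all 384 analysed, the design tolerates a fall to 21–22%, and at 20% it is only 1–3 points short of 90%. This stands, and it is why both sample sizes must be shown. It does not rescue the claim as written, because the 20% margin is assigned to exclusion and loss to follow-up, not to a lower death rate.

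The size of the fall is also unknown. The Limitations section says only that deaths may be excluded. The registry's 20% concerns surgical patients, whereas this trial takes both type A and type B dissection. It is a benchmark, not an estimate for this population. The source of the 27.4% is not at hand, so the point from which it counts deaths cannot be checked. All of this stands.

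Three stronger readings are tempting, and the document does not support them:

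- **That the trial is shown to be underpowered.** No mortality rate is given for the enrolled population, so a shortfall is a risk of unknown size, not a fact.
- **That a null result would be taken as proof of no benefit.** The Limitations and Discussion say otherwise: after a safe but null result the question would be pursued in a further study. The Limitations section also calls the trial exploratory.
- **That the remark "any possible effects may not be very significant" contradicts the planned effect size.** That is a general caveat, not an estimate, and the effect size is a separate matter from the control rate.

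**Conclusion.** The concern holds in a limited form. The Sample size section states 90% power without condition on a control rate for the disease in general, while the protocol's own account of entry points to lower mortality among those enrolled. The 90% is therefore not supported for this population.

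How much is lost depends on two unknowns: control mortality after randomisation, and how many of the 384 are analysed. At 20% control mortality, power lies between 79% (307, Freedman) and 89% (384, exact chi-square). Losses larger than that need control rates of 15% or 10%, which are assumptions.

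The figures also assume that the hazard ratio stays at 0.4135. If the absolute difference stayed at 15 points instead, power would rise. From a 20% control rate, however, that means a fall to 5%, a 75% relative reduction (15/20) against the planned 55% (15/27.4).

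**What to change.** In the Sample size section:

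1. State that the 90% holds only if control mortality counted from randomisation is 27.4%, with the stated hazard ratio and 307 evaluable patients.
2. Give power at lower control rates, for example 20%, 15% and 10%, for both 307 and 384 analysed, labelling these rates as assumptions.
3. Justify the planning rate for patients who reach oral intake, with deaths counted from that point. The centre's 2013–2018 records, already used under Follow-up for length of stay, are the natural source if they show when oral intake began.

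Enrolment, endpoint and analysis stay as they are. The cost is a revised paragraph, a look at existing records, and a stated power that is less favourable than 90%.

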### Data collection and management

At enrollment, we will collect the demographic information of the participants, including age, gender, blood pressure, heart rate, previous disease history, medical history, smoking history. Leukocytes, hemoglobin, platelets, C-reactive protein, cholesterol, triglycerides, creatinine, uric acid, glycosylated hemoglobin, AST, and ALT will be measured at baseline, the 7th, and 13th day. Here, 2 mL fasting venous blood will be taken for measurement in the morning. All these blood parameters will be collected. At discharge or death of the patient, data will be collected on patient status, medication in the hospital, diagnosis and comorbidity. All data will be transferred to a database by duplicate entry using EpiData software (Denmark, version 3.1), and will be stored in the scientific research platform of the First Affiliated Hospital of Shantou University Medical College, which is a secure server with limited access and supported for anonymity, analysis and review.

### Outcome measurements

The primary outcome of this study will be the in-hospital mortality at 30 days. We will calculate in-hospital mortality by counting all-cause death. Secondary outcome will be the incidence of liver dysfunction, as measured through ALT and AST at the 7th and 13th day. The expected trial target is fewer deaths in the statin group compared to the control group.

### Statistical and analytical plans

A comprehensive statistical analysis plan will be prepared before database locking. All analyses will be conducted according to the intention-to-treat (ITT) principles. The primary outcome is binary, it will be expressed as frequency and percentage, a chi-square test will be used to analyze. All statistical analyses will be two-sided, and statistical significance will be set at 0.05. Continuous data such as blood pressure, heart rate and blood parameters, will be presented as mean ± SD; Categorical data, such as previous disease history and smoking history, will be expressed as frequency and percentage of patients in each category. The Kolmogorov-Smirnov test will be used to confirm the normality of the distribution of continuous data, if *P* < 0.05 indicates the data is not normally distributed, advanced raw data conversion (such as logarithmic conversion) will be performed to see whether the data conform to a normal distribution. If not, the rank-sum test will be selected. Otherwise, Student’s *t* tests will be used for continuous data. The chi-square test will be used for categorical data. Survival curves will be determined by the Kaplan-Meier method for survival analysis. The difference in changes between the groups will be analyzed using both Student’s *t* test and analysis of covariance to adjust for the baseline values. A *p* value of < 0.05 will be used to indicate statistical significance. The missing data will be handled by using Mean/Mode Completer. If the missing data is numerical, it will be filled according to the average value of all other objects; if the missing data is non-numerical, then it will be supplemented by the value with the most frequent value of all other objects according to the mode principle in statistics. SPSS statistical software (SPSS Inc., Chicago, IL, USA, version 23) will be used for statistical analysis.

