### Randomization and allocation

According to the order of the participants enrolled, they will be randomly assigned to the control or statin group by using a corresponding random number and envelope method for allocation concealment (patients will be assigned to a corresponding group according to the allocation sequence in an envelope that will be distributed to the research implementation personnel after the allocation sequences are packed in an opaque envelope by separate staff). Balance in allocation across the study participants will be enhanced through stratification by the type of AAD (two types: type A, type B). To avoid the imbalance caused by simple randomization, we introduce block randomization. The block length was 4 with two groups in this study (statins group and control group). The allocation sequence will be generated at a 1:1 (statin/control) ratio using the random number generator in the SPSS statistical software package (SPSS Inc., Chicago, IL, USA, version 23) (Fig. 1).

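### Randomisation is stratified by dissection type but the named primary test is an unstratified chi-square: slightly conservative if type is prognostic, and easily aligned with the design

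*Protocol article*

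**What the plan says.** Under Randomization and allocation, the protocol article names one stratification factor: "Balance in allocation across the study participants will be enhanced through stratification by the type of AAD (two types: type A, type B". Allocation within type is by permuted blocks: "The block length was 4 with two groups in this study (statins group and control group". The ratio is equal: "The allocation sequence will be generated at a 1:1 (statin/control) ratio".

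Under Outcome measurements, the endpoint is fixed: "The primary outcome of this study will be the in-hospital mortality at 30 days", counting deaths from any cause. Under Statistical and analytical plans, the test is fixed: "The primary outcome is binary, it will be expressed as frequency and percentage, a chi-square test will be used to analyze". The error rate is set in the same section: "All statistical analyses will be two-sided, and statistical significance will be set at 0.05".

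No stratum term, stratified test or adjusted model is named for mortality. The only adjustment in that section concerns changes between groups, which are to be "analyzed using both Student’s *t* test and analysis of covariance to adjust for the baseline values". That covers neither the primary outcome nor dissection type. The section also promises a full analysis plan before database lock. The Sample size calculation is unstratified.

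**The concern.** Blocking within type removes most of the chance imbalance in type between the arms. A plain chi-square is calibrated for a design in which that imbalance can occur, so its standard error includes variability that the design has already removed. When mortality differs between type A and type B, the test rejects less often than its nominal 5% under the null and has somewhat less power under the alternative.

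What is at stake is modest: some precision that the stratified design has already made available. It matters more if the true effect is smaller than planned. The Limitations section itself allows for this when it says that effects at the chosen dose may not be pronounced.

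**Working it through.** **1. The plan's own figure.** Inputs from Sample size: mortality 27.4% (control) and 12.4% (statin), 90% power, two-sided 0.05, Freedman log-rank method.
- Hazard ratio = ln(1 − 0.124) / ln(1 − 0.274) = 0.4135, as stated.
- Events = (1.960 + 1.2816)² × [(1 + 0.4135) / (1 − 0.4135)]² = 61.02.
- N = 2 × 61.02 / (0.274 + 0.124) = 306.6, so 307. Then 307 / 0.80 = 383.75, so 384.

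Both totals reproduce. With the same two rates, the standard two-proportion formula for a plain chi-square gives 91.2% power at 153 per arm and 96.0% at 192 per arm.

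**2. Assumptions.** The article does not give the share of type A or mortality by type. Assumed here: share of type A π = 0.60, with control mortality pA vs pB of 35% vs 15% or 40% vs 8%. Overall control mortality is then 0.6 × 0.35 + 0.4 × 0.15 = 27.0%, or 0.6 × 0.40 + 0.4 × 0.08 = 27.2%, close to the planned 27.4%.

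**3. True level by formula.** The share of outcome variance that lies between types is s = π(1 − π)(pA − pB)² / [p(1 − p)], where p is overall mortality. The true level of the plain test is about 2 × [1 − Φ(1.96 / √(1 − s))].
- 35% vs 15%: s = 0.24 × 0.04 / 0.1971 = 0.049. The effective critical value is 1.96 / √0.951 = 2.010, and the level is 0.044.
- 40% vs 8%: s = 0.24 × 0.1024 / 0.1980 = 0.124. The effective critical value is 1.96 / √0.876 = 2.094, and the level is 0.036.

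**4. True level by simulation.** With blocks of four within type, the plain chi-square had a level of about 0.045 and 0.037. The Cochran-Mantel-Haenszel (CMH) test stratified by type had 0.050 in both cases. The simulated values sit slightly above the formula because unfinished blocks leave a small residual imbalance.

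**5. Power by simulation.** A common odds ratio was chosen to give the overall statin mortality shown, with 200,000 trials per scenario.

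| Control mortality A vs B | Statin mortality | N | Chi-square | CMH | Loss (points) |
|---|---|---|---|---|---|
| 35% vs 15% | 12.4% | 308 | 91.1% | 91.5% | 0.4 |
| 35% vs 15% | 12.4% | 384 | 95.8% | 96.1% | 0.3 |
| 40% vs 8% | 12.4% | 308 | 92.3% | 93.4% | 1.1 |
| 40% vs 8% | 12.4% | 384 | 96.6% | 97.3% | 0.7 |
| 35% vs 15% | 17.4% (assumed) | 307 | 53.1% | 54.6% | 1.5 |
| 35% vs 15% | 17.4% (assumed) | 384 | 62.5% | 64.2% | 1.7 |
| 40% vs 8% | 17.4% (assumed) | 307 | 54.8% | 58.8% | 4.0 |
| 40% vs 8% | 17.4% (assumed) | 384 | 64.9% | 68.8% | 3.9 |

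A repeat simulation agreed to within about 0.3 points in every cell. Its smallest loss at the 10-point effect was 1.4 points.

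**6. Sensitivity to the assumptions.** With a 50:50 type mix, overall control mortality held at 27.4% and N = 307:
- Control mortality 35% vs 19.8%: chi-square level 0.048; power 92.0% against 92.2% for CMH.
- Control mortality 50% vs 4.8% (the extreme case): chi-square level 0.023; power 93.8% against 95.9% for CMH.
- No difference between types: both tests have a level of about 0.05 and practically equal power.

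**The case against.** **The analysis plan could settle it.** The article is a condensed document and promises a full analysis plan. That would answer a complaint that something was missing. Here the article names the primary test, and a stratified test introduced later would depart from it. The point therefore stands.

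**The test is valid and the trial keeps its power.** This is correct. A reader might infer from a level that is off 5% that false positives are inflated, or that the trial is underpowered. Neither is supported. In every scenario with a mortality difference between types the level was below 5%, so a significant chi-square result would remain sound. Power at the planned effect stays above 90%.

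**The size is assumed.** Also correct. The stated purpose of stratifying is balance; that type is strongly prognostic is an inference. The Limitations section says that patients who die early, or before eating resumes after surgery, may not be enrolled. That could narrow the gap between types. Confidence is high for the mismatch, not for its size.

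**The missing interval.** A reader might go further and say that the article wrongly omits an effect estimate and interval, and so plans to read a null result as proof of no harm. The documents do not support this. Interval reporting is commonly left to the analysis plan. The remarks in Limitations and Discussion about mortality not being increased are conditional talk about a later study, not a decision rule. Stratification would also change little there. With 27.4% in both arms the 95% half-width is 1.96 × √(2 × 0.274 × 0.726 / 153.5) = 10.0 points at 307 patients, and 8.9 points at the 384 to be enrolled. Stratifying would reduce the 10.0 only to 9.7 or 9.3 points in the two scenarios. An interval is worth adding, as advice and not as a finding.

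**Conclusion.** The mismatch between the stratified randomisation and the unstratified primary test is plain in the text, and the direction of its effect is certain if mortality differs by type: the test is slightly conservative and gives up some precision. Under the 60% type A assumption and the two mortality gaps examined, the true level is about 4.5% to 3.7%. The power loss is about 0.3 to 1.1 points at the planned 15-point effect and about 1.4 to 4 points at an assumed 10-point effect. The loss grows with the gap between types and vanishes without one. This is a worthwhile improvement that needs no further patients. It does not threaten the validity of a positive result.

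**What to change.** Amend the primary-outcome sentence under Statistical and analytical plans to say, in substance: 30-day in-hospital mortality will be compared with a CMH test stratified by dissection type (A, B), two-sided at 0.05; the effect estimate will be the type-stratified risk difference with its 95% confidence interval; an unstratified chi-square will be reported as supportive. Stating that the CMH test decides significance avoids ambiguity between it and the estimate.

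The cost is one or two sentences through the route in the Amendment section, made before results are known; Trial status describes the trial as recruiting. Type must already be known to randomise a patient, so no new data are needed. The planned software, SPSS, offers the test, and the risk difference is a weighted average of the differences in two 2 × 2 tables. The sample size need not change.

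### The primary mortality test leaves the collected baseline values unused; it is valid and adequately powered, but pre-specified adjustment would gain a little power at almost no cost

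*Protocol article*

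**What the plan says.** All four points are in the Methods of the protocol article.

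- **Endpoint** (Outcome measurements): "The primary outcome of this study will be the in-hospital mortality at 30 days", counting deaths from any cause.
- **Primary test** (Statistical and analytical plans): "The primary outcome is binary, it will be expressed as frequency and percentage, a chi-square test will be used to analyze". Neither a covariate nor the stratification factor is mentioned.
- **Baseline data** (Data collection and management): at enrolment, "we will collect the demographic information of the participants, including age, gender, blood pressure, heart rate, previous disease history, medical history, smoking history". Leukocytes, hemoglobin and platelets are also taken at baseline, and the same sentence continues: "C-reactive protein, cholesterol, triglycerides, creatinine, uric acid, glycosylated hemoglobin, AST, and ALT will be measured at baseline, the 7th, and 13th day".
- **Randomisation** (Randomization and allocation): "Balance in allocation across the study participants will be enhanced through stratification by the type of AAD (two types: type A, type B").

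The only baseline adjustment in the analysis section is this: "The difference in changes between the groups will be analyzed using both Student’s *t* test and analysis of covariance to adjust for the baseline values". It concerns changes in continuous measures and cannot be applied to death. The same section announces a fuller analysis plan before database lock.

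**The concern.** Baseline adjustment is planned for changes in continuous measures, which are not among the trial's stated outcomes, while the mortality comparison that decides the trial has none. If the recorded values predict early death, an unadjusted test gives up some power and leaves the estimate more exposed to chance imbalance in risk, with only some 61 to 76 deaths expected.

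This would matter most if the true effect were smaller than the 15-point reduction used for sizing. The Limitations section allows for that: it concedes that the effect at the chosen dose may be modest, and that the enrolment conditions may lower the observed mortality.

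The announced analysis plan does not remove the point, because the article already names the primary test. What is questioned is a stated choice, not a missing detail.

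**Working it through.** **Inputs from the article (Sample size).** Mortality 27.4% (control) and 12.4% (statin); two-sided alpha 0.05; power 90%; log-rank test by Freedman's method; 307 before and 384 after a 20% allowance.

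**Assumed, because the documents give no figure.** The prognostic strength of the baseline values, and a smaller effect of 27.4% v 15%.

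**1. The plan's own figures reproduce.**
- Hazard ratio = ln(1 - 0.124) / ln(1 - 0.274) = 0.4135.
- Freedman events = (1.960 + 1.282)² × [(1 + 0.4135)/(1 - 0.4135)]² = 61.0.
- Mean event rate = (0.274 + 0.124)/2 = 0.199, so N = 61.0/0.199 = 306.6, that is 307.
- 307/(1 - 0.20) = 384.
- Expected deaths: 307 × 0.199 = 61 and 384 × 0.199 = 76.

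**2. Power of the planned chi-square.** With n per arm, d = p1 - p2 and m = (p1 + p2)/2:

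power = Φ[(d - 1.96 × SE0)/SE1], where SE0 = √(2m(1 - m)/n) and SE1 = √((p1(1 - p1) + p2(1 - p2))/n).

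- N = 307 (n = 153.5): SE0 = 0.0456, SE1 = 0.0448, so Φ(1.36) = 91.2%.
- N = 384 (n = 192): SE0 = 0.0407, SE1 = 0.0400, so Φ(1.75) = 96.0%.

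**3. Approximate effect of adjustment.** If the covariates explain a share R² of the outcome variance, multiply both variances by (1 - R²). Results are power in %; the last column is the 95% CI half-width for the risk difference at 384 under the planned effect, in percentage points.

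| Assumed R² (c-statistic) | 12.4%, N = 307 | 12.4%, N = 384 | 15%, N = 307 | 15%, N = 384 | Half-width |
|---|---|---|---|---|---|
| 0 (unadjusted) | 91.2 | 96.0 | 76.0 | 84.7 | 7.8 |
| 5% (about 0.63) | 92.5 | 96.8 | 78.1 | 86.5 | 7.7 |
| 10% (about 0.70) | 93.8 | 97.5 | 80.3 | 88.2 | 7.4 |
| 17.5% (about 0.76) | 95.5 | 98.3 | 83.6 | 90.8 | 7.1 |

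**4. Simulation** (3,000 trials per scenario, chi-square against adjusted logistic regression).
- Four covariates, N = 307, combined c-statistic 0.69, 0.74 or 0.79. At the planned effect, power goes from about 92% to 93, 94 and 96%. At 27.4% v 15%, it goes from about 77% to 80, 82 and 86%.
- One covariate, planned effect, 192 per arm. At c about 0.63, 0.70 and 0.76, power goes from 95.7 to 96.6%, 95.9 to 97.3%, and 96.1 to 98.3%.
- At c about 0.63 and 154 per arm, it goes from 91.6 to 92.3%.
- A test based on the standardised risk difference has the same power as the test of the model coefficient, so reporting a marginal effect loses nothing.

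**5. Type I error and cost if the covariates are weak.** With no treatment effect, both analyses reject in about 4-6% of trials (simulation error about 0.4 points). With one covariate of no prognostic value at 192 per arm, power is 96.0% either way; with four more such covariates it is 95.9%.

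**6. Room in the model.** Arm, dissection type and four baseline values make six terms: 61/6 = 10 to 76/6 = 13 expected deaths per term. That supports a short list, not every variable collected.

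**7. Not computed.** All comparisons above are against a plain chi-square. The increment beyond an analysis adjusted for dissection type alone was not separated out.

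**The case against.** The strongest reply is that nothing here is wrong. A chi-square test on a binary outcome is valid, the sample size reproduces, and the power target is met. Those points stand.

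The relevant N is also arguably 384. The analysis follows intention to treat, and in-hospital death under daily follow-up should rarely be missing. At 384 the planned effect already has 96% power, so there is little left to gain. That stands too.

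A reader might go further than the documents allow in three ways:
- **That risk of early death varies widely in this trial, so substantial precision is being thrown away.** No section gives the prognostic strength of any baseline value. The requirement that patients can take oral medication, and the remarks in Limitations about critically ill patients being missed, point if anything to a narrower range of risk.
- **That the whole gain is separate from the stratification factor.** It may partly overlap with it.
- **That the covariates could be chosen from the centre's 2013-2018 patients.** The Follow-up section gives only their average length of stay and does not show that usable covariate and outcome data exist.

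It is also fair to say that changing the primary analysis during an open-label trial invites suspicion. The Blinding section leaves assessors and analysts unblinded, and Trial status reports recruitment in progress. That is a reason to fix the list formally and early; it does not remove the benefit.

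**Conclusion.** The point holds as an efficiency improvement to a stated method. It does not support a claim that the primary test is invalid, that the trial is underpowered on its own assumptions, or that the deciding result is seriously compromised.

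Over an assumed combined c-statistic of about 0.6 to 0.79, the gain at the planned effect is about 1-4 points of power at 307 patients and 0-3 points at 384. At 27.4% v 15% it is about 0-9 points. These ranges rest on assumed prognostic strength, and for the smaller effect on an assumed statin mortality as well. What favours the change is the balance: no inflation of type I error, almost no loss if the covariates prove weak, and no new data.

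**What to change.** In Statistical and analytical plans, make the primary analysis a logistic regression of 30-day in-hospital death on arm, dissection type and about four named baseline values. An example list is age, systolic blood pressure, creatinine, and either hemoglobin or C-reactive protein. Base both the test and the 95% confidence interval on the standardised (marginal) risk difference, which reads as easily as two percentages. Keep the chi-square test as a sensitivity analysis.

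**Cost.** One paragraph and a dated protocol amendment; no extra patients, visits or measurements. The covariates must be chosen on clinical grounds and fixed before anyone compares outcomes by arm. The model is slightly harder to explain than a 2×2 table.
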